### Patient selection

Patients with the diagnosis of intracerebral metastasis on contrast-enhanced MRI will be evaluated and screened for the protocol. All patients fulfilling the inclusion and exclusion criteria will be informed about the study. Registration for the study must be performed prior to the initiation of RT. The study treatment (neoadjuvant SRS and/or neurosurgical intervention) should be initiated no later than 3 weeks after diagnosis of intracerebral metastases.

Patients meeting all of the following inclusion criteria will be considered for admission to the trial:Patients with 1–4 intracerebral metastases observed on contrast-enhanced MRI from histologically confirmed solid tumors.One intracerebral metastasis is ≥ 3 cm in diameter orPersisting neurologic symptoms or symptomatic epilepsy from intracerebral metastases despite treatment with steroids.Tumor location close to eloquent brain areas therefore neurological symptoms can be expected without long-term steroidal medication.Patient decides to undergo surgical intervention, if resection and radiotherapy are equal treatment options or if the patient declines radiotherapy.
Age ≥ 18 years of age.Karnofsky performance score ≥ 70, Eastern Cooperative Oncology Group (ECOG) performance score ≤ 1.Women with childbearing potential should have adequate contraception.Ability of subject to understand character and individual consequences of the clinical trial.Written informed consent (must be available before enrolment in the trial).

Patients presenting with any of the following exclusion criteria will not be included in the trial:Patients with unknown primary tumor.The diameter of any single lesion exceeding 4 cm.Tumors causing severe neurological deficits or with mass effect requiring immediate surgical intervention.Previous radiotherapy to the brain.Known histological type of small cell cancer, germ cell cancer, or lymphoma.Patient refuses to take part in the study.Patients who have not yet recovered from acute toxicities of prior therapies.Clinically active renal, liver, or cardiac disease.Known carcinoma within 5 years (excluding carcinoma in situ of the cervix, basal cell carcinoma, squamous cell carcinoma of the skin) requiring immediate treatment that interferes with the study therapy.

### Radiotherapy

#### Treatment planning

All patients will be prepared for highly advanced SRS. Individual mask fixation will be performed for each patient. Computed tomography (CT) with and without contrast enhancement will be performed with the patient in individual mask fixation. Additionally, MRI with and without contrast enhancement will be performed for target volume delineation.

#### Target volume delineation for neoadjuvant SRS

Gross target volume (GTV)—macroscopic lesion visible on MRI with T1-weighted contrast enhancement.

Clinical target volume (CTV)—GTV plus a safety margin of 2 mm accounting for microscopic spread.

Planning target volume (PTV)—CTV plus a margin of 1–3 mm accounting for movement and positioning inaccuracies.

#### Dose prescription

Neoadjuvant SRS is applied in a single fraction with single doses depending on the volume and location of the intracerebral metastases requiring neurosurgical resection. The starting dose for the dose escalation scheme will be the dose used by Asher et al. [21] that was already proven to be safe and tolerable in a neoadjuvant setting. The dose will be increased by 2 Gy increments up to the dose recommended by the DEGRO working group on SRS for intracerebral metastases (Table 1) [25]. Doses are prescribed to the 80% isodose line using a linear accelerator.

**Table 1 Tab1:** Cohorts and neoadjuvant SRS dose levels in the present study

Cohort	SRS dose level (Gy)		
	I	II	III
Lesion of ≤ 1.0 cm	18	20	22
Lesion of 1.1–2.5 cm	16	18	20
Lesion of 2.6–3.0 cm	14	16	18
Lesion of 3.1–4.0 cm	12	14	16

The patients will be assigned to 4 different cohorts depending on the largest diameter of the intracerebral metastases to be radiosurgically treated before surgical removal. Each cohort has 3 dose levels. Size and dose were chosen according to the recommondations of the German Society of Radiation Oncology (DEGRO) working group on SRS for intracerebral metastases. The first 3 patients in the first cohort will be treated at a starting dose. If no dose-limiting toxicity (DLT) occurs in that dose level, the following 3 patients will be treated at the next higher dose level; if any of the first 3 patients experiences a DLT, the following 3 patients will be treated at the same dose level. At the highest dose level, at least 6 patients will be treated. Dose will be prescribed to the 80% isodose for linear accelerator (LINAC)-based radiotherapy

*SRS* stereotactic radiosurgery

If further metastases are present (up to 4 in total, no lesion exceeding 4 cm in diameter) that do not require resection, those lesions will be treated with SRS according to the guidelines of the DEGRO working group on SRS for intracerebral metastases [25]. Quantitative analysis of normal tissue effects in the clinic (QUANTEC) reports are applied for dose constraints of normal tissues [26, 27].

### Neurosurgery

For optimal surgical planning, all patients will have an MRI for navigation purposes. For eloquent lesions (less than 2 cm distance between the metastases and the corticospinal tract or the Broca’s area), intraoperative neuromonitoring utilizing direct cortical and subcortical electrical stimulation and navigated transcranial magnetic stimulation will be performed to minimize the risk of new neurological deficit [28–31]. Tumor resection will be carried out according to microsurgical standards. Surgical parameters, such as estimated blood loss, duration of surgery, need for blood transfusions, and complications will be documented in a standardized fashion. To reflect the daily practice and not the best surgical approach for individual cases, there will be no mandate on a specific surgical approach, and each center will decide the surgical approach independently. For the same reasons, individual surgical experience cannot be taken into consideration, but experienced centers have been selected. Postoperative MRI for resection control will be done in all patients, thereby special emphases will also be drawn for postoperative ischemia. Postoperative care is not standardized in the study protocol. The use of analgesics and cortisol follows the local routine, but needs to be documented.

### Sample size calculation

Sample size was determined using the traditional “3 + 3” design as explained below. As radiation dose will differ according to the lesion size, 4 independent cohorts of patients will be evaluated for each lesion size/dose level. With 3 dose levels in 4 different cohorts according to the lesion size, this will lead to a minimal sample size of 4 × [(3 × 3) + 3] = 48 patients, assuming that at least 6 patients should have been tested at MTD in each cohort and that no DLTs occur. In case of DLTs in any patient of a certain dose level group, the size of this group will be enlarged to 6 patients. Therefore, the final sample size might vary.

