
This trial aims to escalate the dose for neoadjuvant SRS up to the dose thresholds depending on tumor size recommended by the German expert group on stereotactic radiation oncology [25]. Given the improved efficacy of systemic cancer therapies, long-lasting local control becomes of growing importance. Since local FSRT aims to prolong the time interval until the application of WBRT, locally efficient doses have to be applied.

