### Statistical analyses

The traditional “3 + 3” design remains the prevailing method for conducting phase I cancer clinical trials [32, 33]. It requires no modelling of the dose-toxicity curve beyond the classical assumption for cytotoxic drugs that toxicity increases with dose. This rule-based design proceeds with cohorts of 3 patients. The first 3 patients in the first cohort will be treated at a starting dose that is considered to be safe based on extrapolation. If none experiences a TLD at that dose level, the following 3 patients will be treated at the next higher dose level. The MTD for which no DLT occur will be evaluated according to the CTCAE Version 5.0 (2017) continuously during the study until first follow up (4–6 weeks after surgery) for each cohort and dose level. A DLT is defined as central nerve system necrosis (≥ grade 3) or cerebrospinal fluid leakage (≥ grade 4) or wound infection (≥ grade 4) or wound dehiscence (≥ grade 4) or postoperative hemorrhage (≥ grade 4) or cognitive disturbance (≥ grade 4) or cerebral edema (≥ grade 4) or headache (≥ grade 4) or seizure (≥ grade 4). If no DLT occurs in one dose level, another 3 patients will be treated at the next higher dose level. However, if any of the first 3 patients experiences a DLT, the following 3 patients will be treated at the same dose level. At the highest dose level, at least 6 patients will be treated. Thus, the maximum number of patients enrolled in this study will be 4 × 6 × 3 = 72. Dose will be prescribed to the 80% isodose for linear accelerator (LINAC)-based radiotherapy. The dose escalation continues until at least 2 patients in a cohort of 3–6 patients experience DLTs (i.e., 33% of patients with DLTs at that dose level). The recommended dose for a future phase II trials is conventionally defined as the dose level just below the toxic dose level.

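### The four size cohorts escalate without reference to each other although most doses recur across them, so a dose declared toxic in smaller lesions may still be opened, and reported as the MTD, in larger ones

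*Protocol article*

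**What the plan says.** The Sample size calculation section says: "As radiation dose will differ according to the lesion size, 4 independent cohorts of patients will be evaluated for each lesion size/dose level". Under Dose prescription, "The patients will be assigned to 4 different cohorts depending on the largest diameter of the intracerebral metastases" that are to be irradiated before removal. Table 1 then gives these dose levels I / II / III:

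| Cohort | I | II | III |
|---|---|---|---|
| "Lesion of ≤ 1.0 cm" | 18 Gy | 20 Gy | 22 Gy |
| "Lesion of 1.1–2.5 cm" | 16 Gy | 18 Gy | 20 Gy |
| "Lesion of 2.6–3.0 cm" | 14 Gy | 16 Gy | 18 Gy |
| "Lesion of 3.1–4.0 cm" | 12 Gy | 14 Gy | 16 Gy |

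The Background ties the ceiling to size: "This trial aims to escalate the dose for neoadjuvant SRS up to the dose thresholds depending on tumor size". Statistical analyses names only one ordering assumption, for the 3+3 design: "It requires no modelling of the dose-toxicity curve beyond the classical assumption for cytotoxic drugs that toxicity increases with dose". That section sets the rules. Three patients are treated per level, with three more after any DLT and at least six at the top level. Escalation ends once two patients in a group of 3 to 6 have a DLT, and the phase II dose is the level below the toxic one. The MTD is evaluated per cohort and dose level. Under Monitoring, an independent DSMB reviews recruitment, adverse events and data quality at least twice a year and makes general recommendations. No rule there links a finding in one cohort to a dose in another.

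**The concern.** Table 1 and the Background imply that a given dose is no better tolerated in a larger lesion than in a smaller one. The decision rules do not use that ordering. Two DLTs at 14 Gy in lesions of 2.6–3.0 cm end escalation in that cohort, yet the cohort of 3.1–4.0 cm may still open 14 Gy and then 16 Gy and report either as its MTD.

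Two things are at stake. The first is safety information: a toxic finding at a dose does not reach the decision to open that dose, or a higher one, in larger lesions. The second is coherence of the primary result: the four MTDs feed the phase II recommendation, and the article does not say how MTDs that run against the size order would be read.

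**Working it through.** **1. The plan's own figures.** Minimum: 4 × [(3 × 3) + 3] = 4 × 12 = 48. Maximum: 4 × 6 × 3 = 72. Both reproduce, so the sample-size arithmetic is not in question.

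**2. Overlap in Table 1.** There are 4 × 3 = 12 cells and six distinct doses (12, 14, 16, 18, 20, 22 Gy). 14 Gy and 20 Gy each occur in two cohorts; 16 Gy and 18 Gy each occur in three. Shared doses fill 2 + 2 + 3 + 3 = 10 of the 12 cells. Pairs of a smaller-lesion and a larger-lesion cohort at the same dose: 1 + 1 + 3 + 3 = 8. Only 12 and 22 Gy are unique.

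**3. One pair, exact.** With true DLT risk p, a level below the top is cleared with no DLT in 3, or with one in the first 3 and none in the next 3:

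P(clear) = (1 − p)³ + 3p(1 − p)⁵

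Given that both cohorts reach the dose at that same p, the chance that it is called toxic in the smaller-lesion cohort and cleared in the larger is [1 − P(clear)] × P(clear):
- p = 0.10: P(clear) = 0.906, and 0.094 × 0.906 = 0.085
- p = 0.20: P(clear) = 0.709, and 0.291 × 0.709 = 0.206
- p = 0.30: P(clear) = 0.494, and 0.506 × 0.494 = 0.250

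Split verdicts on one dose are thus common even when the true risk is identical.

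**4. Whole trial, simulated.** The article gives no DLT rates, so these are assumptions. Four independent cohorts follow the stated rules, with six patients at level III, level III taken as the MTD if it is not toxic, and 20,000 trials per scenario. Risks at levels I/II/III are the same in every cohort, which makes a given dose riskier in larger lesions, in line with Table 1.

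| Assumed risk at I/II/III | A dose called toxic in smaller lesions is at or below the MTD in a larger-lesion cohort | A larger-lesion cohort ends with a strictly higher MTD |
|---|---|---|
| 1/2/5% | about 2% | about 1% |
| 2/5/10% | about 8% | about 7% |
| 5/10/20% | about 23% | about 16% |
| 10/20/30% | about 38% | about 21% |
| 15/25/35% | about 40% | about 15% |

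The last column is smaller because it needs an MTD in both cohorts and a strict reversal. Requiring six patients at every MTD, as the sample-size section assumes, moves the results by at most about two percentage points.

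**5. What the toxic calls represent.** In the first four rows every true risk is 30% or less, below the 33% that the plan attaches to a toxic level. Every toxic call in those rows is therefore a chance result in 3 to 6 patients. In the last row only level III, at 35%, exceeds that mark.

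**6. Effect of an order constraint.** At 5/10/20%, isotonic estimation over dose and size cut contradictory MTD pairs from about 24% to about 4% in a separate simulation run. Correct MTD selection was practically unchanged (58% against 57%).

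**The case against.** One 3+3 design per stratum is a recognised choice, and the sample-size sentence gives lesion size as the very reason for separate cohorts. A reader might infer that the word independent contradicts Table 1. It does not: no two statements conflict, and ordering by size is implied by Table 1 and the Background rather than stated as an assumption. That objection stands.

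A reader might also infer that most trials would expose patients with larger lesions to a dose already known to be toxic. The same simulation has a larger-lesion cohort treated at or above a dose called toxic in smaller lesions in about 66% of trials at 10/20/30% and 78% at 15/25/35%. The documents do not support reading these as harm, for three reasons:
- Eight of the nine DLT categories need grade 4 or higher within a window that closes 4–6 weeks after surgery, and the starting dose is described as already shown to be tolerable. Nothing in the article supports risks that high. At 2/5/10% the figure is about 9%.
- Most of the toxic calls are chance results, as shown above.
- Calendar order is not modelled. A lesion of at least 3 cm is one of the listed selection criteria, so larger-lesion cohorts may fill early and the treatment may precede the toxic finding.

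Finally, there is oversight: an independent DSMB, a single centre and study-group meetings. The article also condenses a fuller protocol. This softens the point but does not remove it. Review at least twice a year is no trigger, and a level can be completed and the next one opened between reviews. The independence of the cohorts is stated in the article, not left out of it.

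**Conclusion.** The point holds as a weakness of the stated rule. Under the text, a dose declared toxic in a cohort of smaller lesions may be opened and reported as the MTD in a cohort of larger lesions, and no step deals with MTDs that reverse the size order. The size depends wholly on assumed DLT risks: about 8% of trials at 2/5/10% and 23% at 5/10/20%, more at higher assumed risks and about 2% at 1/2/5%. These figures assume equal risks by level across cohorts, describe end-of-trial results regardless of calendar order, and mostly reflect chance in groups of 3 to 6. They show how often the results could be incoherent, not how often patients would be harmed. The change is worth making because it is cheap and the primary result depends on it.

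**What to change.** Reconcile the Sample size calculation section with Table 1 in three steps:

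1. State that the cohorts escalate separately, but that a toxic finding at a nominal dose is notified promptly to the existing DSMB and reviewed before the same or a higher dose is opened or continued in a cohort of larger lesions. The clinical consequence stays with the sponsor and the DSMB.
2. Keep the raw 3+3 MTD of each cohort as the primary result.
3. Add a supplementary summary of the DLT counts under the ordering by dose and size, for example by isotonic regression. It should flag any inverted MTDs, to be reconciled before a phase II dose is recommended. Present its gain as coherence, not as better selection of the MTD.

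The cost is a few sentences of protocol text, one extra analysis and an ad hoc notice to a board that already exists. The 48-patient total without DLTs and the maximum of 72 do not change: no review is triggered without a DLT, and a review adds no dose level. The downside is an occasional pause in a larger-lesion cohort, often after a toxic call that arose by chance.

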The primary endpoint of this study is safety assessed from the start of radiotherapy until the first follow up after surgery (4–6 weeks after surgery). Based on experience from clinical practice, the number of patients lost to follow-up is expected to be very small. Patients who dropped out of the study between radiation treatment and first follow-up visit will be replaced by a new patient. For patients without a final examination after 1 year, the last valid examination will be used for the assessment of secondary endpoints. All secondary endpoints will be analyzed in an explorative manner using appropriate statistical methods: Mann–Whitney *U* Test (acute toxicity of CTCAE grade 1–3; late toxicity of CTCAE grade 1–5, immunological parameters, time interval between treatment initiation and start of systemic chemotherapy), Fisher’s exact test or Chi-square test (local control rates), log-rank test and Kaplan–Meier curves (OS and PFS at 12-month follow-up), Student *t* test (neurocognitive function), and scaled *t* test (health-related QoL) for independent patients.

The following parameters will be collected and taken into account in analyses applying regression models: age, Karnofsky performance score, extent of neurosurgical resection, recursive partitioning analysis (RPA)-classification.

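### The sample size assumes six patients at the MTD in every cohort, but the rules guarantee six only at the highest dose level; 48 is the no-DLT size, not the minimum.

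*Protocol article*

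**What the plan says.** All references are to the Methods of the protocol article.

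- **Sample size calculation.** There are four size cohorts with three dose levels each, and "this will lead to a minimal sample size of 4 × [(3 × 3) + 3] = 48 patients". The figure is conditioned: "assuming that at least 6 patients should have been tested at MTD in each cohort and that no DLTs occur". A DLT in a dose-level group enlarges that group to six, and "Therefore, the final sample size might vary".
- **Statistical analyses, escalation.** "If no DLT occurs in one dose level, another 3 patients will be treated at the next higher dose level". Any DLT among the first three leads to three more patients at the same level. Escalation ends at two or more DLTs among three to six patients, and the dose recommended for phase II is the level just below the toxic one.
- **Statistical analyses, six-patient rule.** "At the highest dose level, at least 6 patients will be treated". The note to Table 1 (Dose prescription) says the same. Neither place attaches a six-patient requirement to a lower level that becomes the MTD.
- **Statistical analyses, maximum and replacement.** "Thus, the maximum number of patients enrolled in this study will be 4 × 6 × 3 = 72". Later in the same section: "Patients who dropped out of the study between radiation treatment and first follow-up visit will be replaced by a new patient".

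**The concern.** The MTD is the primary endpoint. The sample size section leads the reader to expect at least six treated patients behind it in each size cohort. The operative rules deliver that only when the cohort reaches level III and tolerates it. When a cohort stops earlier, the recommended dose may have been given to three patients, half the stated basis, and a team following the printed rules would have no instruction to add more.

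Calling 48 minimal raises a second, smaller problem. The section mentions DLTs only as something that enlarges a group. Under the stopping rule they can also end a cohort early, so the trial can be smaller than 48.

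**Working it through.** **Stated figures.** No DLT: 3 + 3 + 6 = 12 per cohort, 4 × 12 = 48. Every level expanded: 6 + 6 + 6 = 18 per cohort, 4 × 18 = 72. Both reproduce.

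**Two readings.** The expansion rule (any DLT leads to three more) and the stopping rule (at least 2 DLTs in 3–6 patients) disagree when 2 or 3 of the first three have a DLT. Reading (a) stops at once; reading (b) always expands to six. Both let escalation continue after one DLT in six, as the stopping rule implies.

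**Paths to an MTD on three patients.**
- Level I 0/3, then level II toxic: the recommended dose is level I, n = 3.
- Level II 0/3, then level III toxic: the recommended dose is level II, n = 3.

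This result needs no assumed DLT rate.

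**How often.** The protocol gives no DLT rates, so p₁/p₂/p₃ are assumptions. Let
- zᵢ = (1−pᵢ)³, the chance of 0/3;
- tᵢ = 1 − (1−pᵢ)³ − 3pᵢ(1−pᵢ)⁵, the chance that level I or II is toxic;
- T₃ = 1 − (1−p₃)⁶ − 6p₃(1−p₃)⁵, the chance of at least 2 DLTs in six at level III.

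Then P(MTD on three) = z₁t₂ + (1−t₁)z₂T₃, the same under both readings.

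- 2/5/10%: 0.941 × 0.027 + 0.995 × 0.857 × 0.114 = 0.025 + 0.098 ≈ 0.12
- 5/10/20%: 0.857 × 0.094 + 0.973 × 0.729 × 0.345 = 0.081 + 0.245 ≈ 0.33
- 10/20/33%: 0.729 × 0.291 + 0.906 × 0.512 × 0.642 = 0.212 + 0.298 ≈ 0.51

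The chance that at least one of the four cohorts ends this way is 1 − (1 − P)⁴: 0.41, 0.79 and 0.94.

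**What three patients can exclude.** With no DLT in n patients, the one-sided 95% upper bound is 1 − 0.05^(1/n): 63% for n = 3 and 39% for n = 6.

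**Smallest evaluable size.**

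| Condition | Reading (a) | Reading (b) |
|---|---|---|
| Printed rules | 4 × 3 = 12 | 4 × 6 = 24 |
| Every cohort yields an MTD | 4 × (3+3) = 24 | 4 × (3+6) = 36 |
| Same, with six at the MTD | 4 × (6+3) = 36 | 4 × (6+6) = 48 |

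**Chance of fewer than 48.** This comes from enumerating every path in one cohort and convolving over four independent cohorts.

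| DLT rates | P(N<48), (a) | P(N<48), (b) |
|---|---|---|
| 2/5/10% | 13% | 7% |
| 5/10/20% | 33% | 20% |
| 10/20/33% | 67% | 47% |

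At 10/20/33% the mean evaluable size is 43.4 under (a) and 46.8 under (b).

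**The case against.** **The 48 carries its conditions.** This is true: the sentence states the no-DLT and six-at-MTD assumptions, and the section warns that the size may vary. If every DLT expands to six, six are treated at the MTD and every cohort yields an MTD, 48 is indeed the floor. The fault is therefore the label, not the sum. But those conditions are not what the printed rules enforce, and a cohort that is toxic at level I yields no MTD and stops at three or six.

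**Three patients at a lower MTD is ordinary in a 3 + 3 design.** Some versions allow it. This protocol, however, says it was sized on six at the MTD in each cohort, so its assumption and its rules disagree.

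**An article condenses the full protocol.** Nothing here rests on an omission. The article prints both the assumption and the rules.

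**The percentages depend on chosen rates.** This stands. The DLTs are grade 4 or worse (grade 3 or worse for necrosis) up to the visit 4–6 weeks after surgery, and the starting dose is described as already shown to be tolerable, so low rates are plausible. At a flat 2%, only about 1% of cohorts have an MTD on three patients and about 3% of trials fall below 48. The contradiction between the sections does not depend on the rates.

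**A stronger reading.** A reader might infer that the planned range is wrong at both ends. The documents do not support that. 72 is the exact ceiling for evaluable patients. It fails only as a count of patients enrolled, because dropouts are replaced. Dropout is expected to be very small, and all 72 places would be filled with a probability of about 1.5 × 10⁻⁶ or less in the three scenarios.

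**Conclusion.** The concern holds for six patients at the MTD, and this should be corrected because it bears on the primary endpoint. By the printed rules an MTD at level I or II can rest on three patients. That happens in 12%, 33% and 51% of cohorts at assumed DLT rates of 2/5/10%, 5/10/20% and 10/20/33%. These figures assume independent patients and cohorts and continued escalation after one DLT in six.

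The label on 48 is also wrong, though less consequential. The rules allow 12 or 24 evaluable patients depending on the expansion reading, and the chance of ending below 48 is 7–13%, 20–33% and 47–67% in the same scenarios. Whether enrolled or evaluable patients are meant by 72 is a minor wording point.

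**What to change.** 1. Reconcile Statistical analyses and the Table 1 note with Sample size calculation. Either the six-patient requirement covers whichever level is declared the MTD, or the sample size section drops that assumption and says that the MTD may rest on three patients.
2. Reconcile the expansion and stopping wording for two or three DLTs among the first three patients.
3. In Sample size calculation, call 48 the size with no DLTs and give the evaluable range that follows from step 2.
4. In the Abstract and Statistical analyses, describe 72 as the maximum of evaluable patients, and let the enrolment figure allow for replacements.

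**Cost.** Steps 2 to 4 need text changes only. If step 1 is resolved by filling the MTD to six, the mean addition is 4 cohorts × 3 patients × P(MTD on three). At 10/20/33% this is 12 × 0.51 ≈ 6 patients: 43.4 to 49.5 under reading (a), 46.8 to 53.0 under reading (b). At 5/10/20% it is 12 × 0.325 ≈ 4, and at 2/5/10% 12 × 0.12 ≈ 1.5. These figures do not count further patients if the added three make that level toxic in turn. The evaluable maximum stays at 72, because no level exceeds six.
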